#### 7.4.1.2 Management of abnormal thyroid function tests

Cediranib therapy has been associated with increases in TSH. In the majority of patients this has not resulted in reductions in either total triiodothyronine (T3) or free thyroxine (T4) to below the lower limit of the normal range, but clinical hypothyroidism has been reported in a small number of patients. Patients have responded to replacement therapy without the need for stopping or reducing the dose of cediranib.

Pharmacological levothyroxine substitution should be given when clinically indicated to normalise the thyroxine level to within the normal range, and before the patient becomes clinically symptomatic. Levothyroxine therapy should also be considered in patients with TSH increases (and thyroxine levels within the normal range), with adverse events and symptoms suggestive of hypothyroidism such as fatigue. Thyroid function and related symptoms should be monitored frequently and the dose of levothyroxine should be titrated as required (Rini et al. 2007).

#### **7.4.1.3 Management of haematological toxicity**

Thrombocytopenia, of CTC grade 1 or 2 in the majority of cases, has also been seen with cediranib monotherapy and combination therapy with other treatments. In view of this finding, close monitoring of platelets at study visits is recommended. Patients with platelet count  $\leq 100 \times 10^9/L$  at baseline should not be included in studies with cediranib and are not eligible for this trial.

Although the effect of short treatment breaks of cediranib on platelet count recovery has not been studied, it is possible that a short break of a few days may help in the situation of CTC grade 3 or grade 4 or prolonged thrombocytopenia. Treatment breaks should be taken at the discretion of the treating clinician and patient response monitored. As guidance, where platelets are  $< 50 \times 10^9/L$  a dose reduction or interruption may be required. Concerns may be discussed with the Chief Investigator.

#### **7.4.1.4 Hypertension management**

Patients will be provided with blood pressure monitors at the beginning of the trial to monitor blood pressure at home on a daily basis and will be encouraged to record this in the patient diaries. Data from the diaries will be used by the site staff to complete the CRFs at each assessment.

**Table 7     Hypertension management protocol for emergent hypertension**

| Hypertension severity                                                                                                                                                                                                                              | Actions                                                                                                                                                                                                                                                                                                                                                                                                                                                                                                                                                                                                                                                                                                                                                                                                                                                                                                                                                                                                                                                                                                                                                                                                                                                                                                                                                                                                                                                                                                                                                                                                                                                                                                                                                                                                                                                                                                                                                                                                                                                                                                                                                                                                                                                                                                                                                                                                                      |
|----------------------------------------------------------------------------------------------------------------------------------------------------------------------------------------------------------------------------------------------------|------------------------------------------------------------------------------------------------------------------------------------------------------------------------------------------------------------------------------------------------------------------------------------------------------------------------------------------------------------------------------------------------------------------------------------------------------------------------------------------------------------------------------------------------------------------------------------------------------------------------------------------------------------------------------------------------------------------------------------------------------------------------------------------------------------------------------------------------------------------------------------------------------------------------------------------------------------------------------------------------------------------------------------------------------------------------------------------------------------------------------------------------------------------------------------------------------------------------------------------------------------------------------------------------------------------------------------------------------------------------------------------------------------------------------------------------------------------------------------------------------------------------------------------------------------------------------------------------------------------------------------------------------------------------------------------------------------------------------------------------------------------------------------------------------------------------------------------------------------------------------------------------------------------------------------------------------------------------------------------------------------------------------------------------------------------------------------------------------------------------------------------------------------------------------------------------------------------------------------------------------------------------------------------------------------------------------------------------------------------------------------------------------------------------------|
| Mild to moderate hypertension:

BP 140/90 mmHg on 2 consecutive occasions >24 hours apart

OR

Increase in diastolic pressure by $\geq 20$ mmHg or to $\geq 100$ mmHg or increase in systolic pressure to $\geq 150$ mmHg | 
 
1. Repeat reading at least 1 hour later. If isolated increase, increase BP monitoring to weekly by health professional or daily home monitoring. Continue all study medication at the same dose.
 
2. If confirmed by second reading, continue all study medication at the same dose and initiate monotherapy with a long acting dihydropyridine calcium-channel blocker (e.g. nifedipine, amlodipine, felodipine) at low dose.
 
3. If calcium channel blocker is contraindicated, use thiazide diuretic or angiotensin converting enzyme inhibitors or angiotensin receptor blockers first line.
 
4. Monitor BP 3 weekly by health professional until it stabilises.
 
5. If BP >140/90 mmHg after 3 weeks INCREASE the first agent to the full dose and consider adding an additional agent in combination (e.g., selective <math>\beta</math>-blocker, thiazide diuretic, angiotensin converting enzyme inhibitors or angiotensin receptor blockers).
 
6. If BP >140/90 mmHg after a further 3 weeks, add an additional agent if the patient is only on one new agent or increase to full doses of the 2-drug combination.
 
7. If BP >160/95 mmHg and is static or increasing after a further 7 days, temporarily stop cediranib and continue anti-hypertensive therapy under close supervision.
 
8. Restart cediranib at the same dose (with maintenance anti-hypertensive therapy) when BP <math>\leq 140/90</math> mmHg. Monitor BP every week until BP stabilised.
 
9. If BP >160/95 mmHg and is static or increasing after 7 days, temporarily stop cediranib and continue anti-hypertensive therapy under close supervision.
 
10. Restart cediranib but at 1 dose lower than the starting dose when BP <math>\leq 140/90</math> mmHg. Monitor BP every week by health professional until BP stabilised.
 
11. If BP increases to >160/95 mmHg, temporarily stop cediranib and continue anti-hypertensive therapy under close supervision
 
12. Restart cediranib but at 2 doses lower than the starting dose when BP <140/90 mmHg. Monitor BP every week until steady state is BP stabilised
 
13. If BP increases to >160/95 mmHg after dose reduction to 15 mg od, despite anti-hypertensive therapy, permanently stop cediranib.
 
 |

| Hypertension severity                                                                                                                                                | Actions                                                                                                                                                                                                                                                                                                                                                                                                                                                                                                                                                                                                                                                                                                                                                                                                                                                                                                                                                                                                                                                                                                                                                                                                                                                   |
|----------------------------------------------------------------------------------------------------------------------------------------------------------------------|-----------------------------------------------------------------------------------------------------------------------------------------------------------------------------------------------------------------------------------------------------------------------------------------------------------------------------------------------------------------------------------------------------------------------------------------------------------------------------------------------------------------------------------------------------------------------------------------------------------------------------------------------------------------------------------------------------------------------------------------------------------------------------------------------------------------------------------------------------------------------------------------------------------------------------------------------------------------------------------------------------------------------------------------------------------------------------------------------------------------------------------------------------------------------------------------------------------------------------------------------------------|
| Severe hypertension:

Increase in diastolic pressure to $\geq 110$ mmHg or increase in systolic pressure to $\geq 180$ mmHg on 2 readings >1 hour apart | 
 
1. Temporarily stop cediranib and consider if hospitalisation is necessary.
 
2. Initiate treatment with a 2-drug combination including a calcium channel blocker licensed for use in severe hypertension, tailored to the patient's underlying conditions and previous anti-hypertension treatment.
 
3. If there is evidence of target-organ damage, intravenous therapy should be considered while continuing oral therapy.
 
4. Nitrates may adversely affect the therapeutic mechanism of action of cediranib but should be used if clinically indicated.
 
5. Restart cediranib at 1 dose lower than the starting dose when BP <140/90 mmHg. Monitor BP every 3 to 7 days until steady state is BP stabilised
 
6. If BP increases to >160/95 mmHg, temporarily stop cediranib and continue anti-hypertensive therapy under close supervision.
 
7. Restart cediranib at 2 doses lower than the starting dose when BP <140/90 mmHg. Monitor BP every week until steady state is BP stabilised.
 
8. If BP increases to >160/95 mmHg after dose reduction to 15 mg od, despite anti-hypertensive therapy, permanently stop cediranib.
 
 |

The development of hypertension in patients treated with cediranib is generally an early event, usually occurring in the first 4 weeks of treatment. In a minority of patients hypertension can also occur later in a treatment schedule.

The rigorous monitoring of BP and adherence to the hypertension management guidelines are necessary in order to achieve optimal hypertension control. Patients on prior anti-hypertension therapy may be particularly at risk of developing moderate or severe hypertension on cediranib. Therefore, patients with pre-existing hypertension or on anti-hypertension medications are likely to benefit from having their BP management optimised before starting cediranib.

For all BP thresholds described in this protocol, a trigger level is considered to be met if either the systolic and/or diastolic pressure reaches the threshold. If the threshold is recorded at home, it must be confirmed by a healthcare professional as defined above before commencing any treatment. CLEAR reasons for progressing to the next step in the management protocol must be documented. When managing mild to moderate hypertension, the following principles should be noted:

- Cediranib may cause rapid increases in BP in some patients
- Calcium-channel antagonists are the first line agents of choice
- Increase anti-hypertensives to maximum doses and add additional agents as required.
- It is recommended that no more than 2 drugs are added in a 48-hour period before temporarily stopping cediranib.

The following cautions and contraindications should be noted:

- Calcium-channel blockers: use with caution in patients with tachyarrhythmias, aortic stenosis, unstable angina or congestive cardiac failure and may cause headache
- Short-acting non-dihydropyridines such as diltiazem or verapamil should be avoided since they may precipitate abrupt fall in BP and increase risk of myocardial ischaemia, infarction or stroke
- Beta-blockers: contraindicated in patients with asthma, chronic obstructive pulmonary disease and A-V block; they should be used with caution in patients with peripheral vascular disease and glucose intolerance and may cause fatigue
- If diuretics are to be used, thiazides rather than loop diuretics are recommended

A record of the management of hypertension will be maintained.

CTCAE grade 3 should NOT be assigned to hypertension AEs on the basis of the number of drugs used according to this protocol to treat mild-moderate hypertension since this is a proactive treatment approach. CTCAE grade 3 should be assigned **if hypertension is not controlled after 7 days of per-protocol anti-hypertensive therapy.**

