#### **7.4.3.2 Management of persistent (>24h) or uncontrolled severe diarrhoea despite loperamide**

- Patients should be advised to stop the cediranib and gefitinib study tablets and care should be taken to prevent dehydration.
- Following evaluation, consider ciprofloxacin for 7 days particularly if the patient has a fever or is neutropenic (although ciprofloxacin is a potential CYP450 inhibitor (see Appendix 3), in this instance it will be given whilst the patient is not on study medication).
- Consider infectious causes and aetiologies such as Clostridium difficile/viral gastroenteritis.

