## Appendix 4: Drugs thought to significantly interact with CYP450 enzymes

These drugs are recommended to be avoided in combination with cediranib and/or gefitinib, and for 2 weeks prior to starting trial treatment.

| Enzyme                  | Potent Inhibitors*                                                                                                                                                        | Potent Inducers**                                                                                        | Substrates†                                                                                                                                      |
|-------------------------|---------------------------------------------------------------------------------------------------------------------------------------------------------------------------|----------------------------------------------------------------------------------------------------------|--------------------------------------------------------------------------------------------------------------------------------------------------|
| CYP1A2                  | Amiodarone,
cimetidine,
ciprofloxacin,
fluvoxamine                                                                                                               | Carbamazepine ,
phenobarbital,
rifampin,
tobacco                                                | Caffeine,
clozapine,
theophylline                                                                                                          |
| CYP2C9                  | Amiodarone,
fluconazole,
fluoxetine,
metronidazole,
ritonavir,
trimethoprim /sulfamethoxazole                                                              | Carbamazepine,
phenobarbital,
phenytoin,
rifampin                                               | Carvedilol,
celecoxib,
glipizide,
ibuprofen,
irbesartan,
losartan                                                                 |
| CYP2C19                 | Fluvoxamine,
isoniazid,
ritonavir                                                                                                                                   | Carbamazepine,
phenytoin,
rifampin                                                                 | Omeprazole,
phenobarbital,
phenytoin                                                                                                       |

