| CYP2D6                  | Amiodarone,
cimetidine,
diphenhydramine,
fluoxetine,
paroxetine,
quinidine,
ritonavir,
terbinafine                                                   | No significant inducers                                                                                  | Amitriptyline,
carvedilol,
codeine,
donepezil,
haloperidol,
metoprolol,
paroxetine,
risperidone,
tramadol                |
| CYP3A4
and
CYP3A5 | Clarithromycin,
diltiazem,
erythromycin,
grapefruit juice ,
itraconazole,
ketoconazole,
nefazodone,
ritonavir,
telithromycin,
verapamil | Carbamazepine,
Hypericum perforatum
(St. John's wort),
phenobarbital,
phenytoin,
rifampin | Alprazolam,
amlodipine,
atorvastatin,
cyclosporine,
diazepam,
estradiol,
simvastatin,
sildenafil,
verapamil,
zolpidem |

\* These will slow down substrate drug metabolism and increase drug effect.

\*\* These will speed up substrate drug metabolism and decrease drug effect

† Exposure, pharmacological action and toxicity may be increased in combination with cediranib and/or gefitinib

This list is not exhaustive and a similar restriction will apply to other agents that are known to strongly induce, inhibit CYP450 enzyme activity or require CYP450 for metabolism. For an extensive list including less significant interactions see <http://medicine.iupui.edu/clinpharm/ddis/table.asp>.

Table compiled from: *Lynch T, Price A. (2007) The effect of cytochrome P450 metabolism on drug response, interactions, and adverse effects. Am Fam Physician. Aug 1;76(3):391-6.*

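### Table 7 names amlodipine as a first-line example with study drug continued, Appendix 4 advises against combining it with the trial drugs, and three cross-references send sites to the wrong appendix

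*Protocol*

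**What the plan says.** **Hypertension plan.** Table 7 in section 7.4.1.4 covers emergent hypertension. At step 2 for mild to moderate hypertension, once a second reading confirms it, sites are to leave study medication unchanged and "initiate monotherapy with a long acting dihydropyridine calcium-channel blocker (e.g. nifedipine, amlodipine, felodipine) at low dose". Step 3 offers other classes where a calcium-channel blocker is contraindicated. Step 5 allows an added agent: a selective beta-blocker, "thiazide diuretic, angiotensin converting enzyme inhibitors or angiotensin receptor blockers". The principles below the table repeat that "Calcium-channel antagonists are the first line agents of choice".

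**Interaction list.** Appendix 4 opens with the statement "These drugs are recommended to be avoided in combination with cediranib and/or gefitinib, and for 2 weeks prior to starting trial treatment". Its substrate column for CYP3A4 and CYP3A5 begins "Alprazolam, amlodipine, atorvastatin". Losartan and irbesartan appear as CYP2C9 substrates and metoprolol as a CYP2D6 substrate. The footnote to that column reads "Exposure, pharmacological action and toxicity may be increased in combination with cediranib and/or gefitinib". The appendix says that its list is incomplete and that a similar restriction applies to other drugs needing CYP450 for their metabolism.

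**Concomitant medication.** Section 7.5 does not put these drugs among those that are forbidden. It places drugs that need P450 for metabolism in a second group, to be used with caution and only where essential.

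**Ciprofloxacin.** Section 7.4.3.2 recognises that this drug is on the interaction list and accepts a 7-day course because "in this instance it will be given whilst the patient is not on study medication".

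**The concern.** A site that treats raised blood pressure from Table 7 and a site that checks a prescription against Appendix 4 get different advice about the same drug. Table 7 presents amlodipine as an ordinary first-line option during continued dosing. Appendix 4 advises against that combination and gives a safety reason for doing so.

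The situation will not be rare. Both arms receive cediranib, and section 2.3.1 lists hypertension among its common side effects. Section 2.4.3.1 reports it among the most common adverse events of the phase I combination study, and section 7.4.1.4 says that it usually appears in the first 4 weeks. What is at stake is the clarity of a safety instruction that many patients are likely to need early, and the consistency with which sites apply it.

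**Working it through.** There is no figure to reproduce. The check sets the texts side by side.

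**1. Is joint use intended?** Yes. Table 7 step 2 keeps all study medication at the same dose when the antihypertensive starts, so the drugs are taken together.

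**2. Which drugs are named in both places?**

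| Table 7, mild to moderate hypertension | Named in Appendix 4? |
|---|---|
| Nifedipine (example, step 2) | No |
| Amlodipine (example, step 2) | Yes, CYP3A4/3A5 substrate |
| Felodipine (example, step 2) | No |
| Angiotensin receptor blockers (class, steps 3 and 5) | Members named: losartan, irbesartan |
| Selective beta-blocker (class, step 5) | Member named: metoprolol |

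So 1 of the 3 first-line examples is on the list by name. A further 3 listed drugs overlap by class only. Carvedilol is also in Appendix 4, but the protocol does not class it as a selective beta-blocker, so it is not counted.

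**3. What status does amlodipine have?** The protocol gives three: a first-line example (Table 7); a drug it advises against combining with the trial drugs (Appendix 4); and, as a P450 substrate, a drug for cautious use where essential (section 7.5).

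**4. Is there an exception that joins them?** None is written. Table 7 does not mention the CYP restriction. Nor does the list of cautions and contraindications for antihypertensives below it. Appendix 4 makes no exception for antihypertensives. For ciprofloxacin, by contrast, section 7.4.3.2 names the conflict and gives a reason for allowing the drug.

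**5. Can a site find the list?** The restrictions at the end of section 5.1.2, section 7.4.3.2 and section 7.5 all cite Appendix 3. That appendix is the table of oral-care products; the interaction list is Appendix 4. The numbering is shifted elsewhere too: sections 7.4.1.5 and 7.4.2.1 cite Appendix 1 for skin care, which is Appendix 2, and section 7.4.1.6 cites Appendix 2 for oral care, which is Appendix 3.

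**6. Does the ciprofloxacin exception hold throughout?** It depends on the patient being off study drug during a 7-day course. Section 7.4.3.4 ties restart to diarrhoea falling to grade 1 or less and does not mention completing the course. If diarrhoea settles before day 7, the two periods could overlap. Section 7.4.3.3 repeats the 7-day course without the off-drug condition.

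**The case against.** The best defence is that section 7.5 already reconciles the texts. It allows such drugs where essential and leaves medication needed for safety to the investigator. Section 7.4.1.4 calls adherence to the hypertension guidance necessary, so use under Table 7 can be read as falling within that allowance. Appendix 4 itself only recommends avoidance. Amlodipine is one of three examples and not the first named, so a site can follow Table 7 without prescribing any drug that Appendix 4 names. All the overlaps are in the substrate column, where the stated worry is greater exposure to the antihypertensive, and Table 7 starts at a low dose with blood-pressure monitoring.

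Most of this stands, and it limits the point. A reader might infer that following Table 7 breaches the protocol, or that Appendix 4 leaves no usable first-line agent; the documents support neither. A reader might also extend the conflict to nifedipine and felodipine through the open-ended clause in Appendix 4, but that needs pharmacology the protocol does not supply. Nor does the protocol show that sites would differ in adverse events or in cediranib interruptions as a result.

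The defence does not remove the inconsistency. The reader has to construct the reconciliation, because neither Table 7 nor Appendix 4 states it, and the pointers that would lead from section 7.5 to the list carry the wrong number.

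On ciprofloxacin, the off-drug condition can be read as covering the whole course, and section 7.1 permits pauses of up to 14 days, long enough to finish 7 days of treatment. Overlap is therefore possible but not required by the text.

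**Conclusion.** The point holds as an inconsistent safety instruction. One drug, amlodipine, is named as a first-line example during continued dosing in one place and advised against in combination in another, with a third status between them. Three more listed drugs overlap by class. Three cross-references to the interaction list are wrong. The ciprofloxacin gap is secondary.

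The number of patients affected cannot be derived. The protocol gives neither a rate of treated hypertension nor the share of patients who would receive a listed drug. The target of 112 patients shows only how many come under Table 7, not how many would meet the conflict.

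The sample size, the primary endpoint and its analysis are unaffected. The conclusion rests only on the wording of the protocol and takes no view on which instruction is clinically right.

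**What to change.** - Reconcile Table 7, the rest of section 7.4.1.4, section 7.5 and Appendix 4 so that each named antihypertensive has one status wherever it appears, with a cross-reference between the hypertension plan and the interaction list.
- Reconcile sections 7.4.3.2 and 7.4.3.3 with section 7.4.3.4 so that the basis for allowing ciprofloxacin and the restart rule agree.
- Change the Appendix 3 references in sections 5.1.2, 7.4.3.2 and 7.5 to Appendix 4, and correct the shifted skin-care and oral-care references in the same pass.

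Which drugs are used, and on what terms, is for the investigators to decide. The cost is protocol wording in one table, a few sections and one appendix. It needs no additional patients or procedures and no change to the analysis.
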